### Process analysis

For process evaluation, the different data sets will be analyzed using a mixed methods approach
[45]. Interviews will be analyzed using qualitative content analysis
[46] based on themes and structure of the CFIR
[43]. Resident records will also be analyzed with qualitative content analysis, but the records will be evaluated using the DCM framework of psychosocial needs
[11] to evaluate the implementation of PCC. Process documents will be analyzed using an Access 2007 database to reconstruct the implementation process. The database will allow frequency and content analysis. Quantitative data sets, including staff questionnaire, structural data, and environmental data, will be analyzed using descriptive statistics. SYMLOG data will be visualized in terms of field diagrams according to the instructions of Bales and Cohen
[44]. To integrate quantitative and qualitative data sets, a side-by-side comparison for merged data analysis
[45] will be performed per institution. Then, the data will be summarized for the 3 study groups accounting for the influencing factors and the degree of implementation. Quantitative and qualitative results will be discussed together and used to confirm or disconfirm each other. Furthermore, the barriers and facilitators of implementation will be merged in an explanatory way to the results on the degree of implementation.

The final step of data analyses will be the merging of outcome data and process evaluation. To avoid bias in interpretation, effect data and data for process evaluation will be analyzed separately by different researchers.

### Economic analysis

Cost-effectiveness analyses focus on the hypothesized additional cost of DCM in comparison to Qol-Assessment using the QUALIDEM. The cost calculation will be performed from a societal point-of-view. Based on the mentioned outcomes, 2 different incremental cost-effectiveness ratios (ICERs) will be calculated: cost per increase in quality of life scores of the residents and cost per increase in attitudes toward dementia scores. Other outcome measures such as challenging behavior, job satisfaction, and burnout will be financially valued and computed on the cost side of the ICER.

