## Abstract

**Background:**

The main objective of care for people with dementia is the maintenance and promotion of quality of life (Qol). Most of the residents in nursing homes have challenging behaviors that strongly affect their Qol. Person-centered care (PCC) is an approach that aims to achieve the best possible Qol and to reduce challenging behaviors. Dementia Care Mapping (DCM) is a method of implementing PCC that has been used in Germany for several years. However, there are no data on the effectiveness of DCM or the challenges of implementation of DCM in German nursing homes.

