## Background

The main objective in providing care for people with dementia is maintenance and promotion of quality of life (Qol)
[1]. Care of nursing home residents with dementia is a challenge for staff, particularly when those residents exhibit challenging behaviors
[2]. The prevalence of challenging behavior in people with dementia is 78% globally
[3]. Similarly,
[4] up to 90% of German residents with dementia have challenging behaviors
[5]. The most frequent symptoms are depressive symptoms followed by aggression
[5]. Challenging behaviors strongly affect the well-being of people with dementia
[6] and have a negative impact on stress levels and job satisfaction of the staff
[2].

Person-centered care (PCC) is described as an approach to achieve the best possible Qol for people with dementia and to reduce challenging behaviors
[7].

There is consensus that PCC focuses on the individuality of the person with dementia and not on his or her impairments
[8-10]. The theoretical underpinning of PCC is Kitwood’s social-psychological theory of personhood
[11]. This theory sets the sense of personal worth, agency, social confidence and hope as global states of well-being for persons with and without dementia. The physical and social environment influence wellbeing and behavior of persons with dementia in a similar way
[12,13]. An appropriate physical environment should provide outdoor space, facilitate orientation, offer different activity areas and enough space to walk around. Social environment factors are e.g. continuity and presence of staff, verbal and nonverbal inclusion of individuals in activities and respectful ways of communication. Internationally, PCC has become an important component of dementia guidelines
[14,15] and research activities
[7,16-18].

The Dementia Care Mapping (DCM), a structured observational assessment instrument, was developed by Kitwood & Bredin
[19] to evaluate and advance the implementation of PCC in institutional and day care settings. The DCM tool was updated by the Bradford Dementia Group to the current 8^th^ version
[20]. DCM is a systematic approach for the assessment of PCC that can help to identify factors influencing behavior and to create individual person-centered care plans
[16,21]. DCM can also be used as an assessment for residents’ well-being and Qol

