**Cost effectiveness**		
**Domain**	**Instrument/source**	**Type of variable**
Resource use	Nursing home administration system	Cost outcome

The data collection times will be oriented with the DCM cycles in the intervention group and will take place before starting the implementation (DCM training) (T0, months 1 to 3) and no more than 2 months after the first (T1, month 9–11) and the third (T2, months 21–23) DCM-cycle. The data collection times for the process evaluation and the implementation process will correspond with T0 to T2 (Figure 
1). Cost data for the economic evaluation will be extracted from the nursing home administrative system at the end of the intervention period.

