### Economic evaluation

The cost-effectiveness of DCM will be investigated by comparing the intervention group with comparison group 2. Data will be extracted from the nursing home administration system. Intervention costs, including costs for the DCM training, will be estimated. Costs that would not occur in routine practice will not be considered in the investigation (i.e., study-specific costs).

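### Pricing challenging behaviour, job satisfaction and burnout into the ICER numerator makes the ratio depend on a chosen price and can count behaviour twice in the quality-of-life ICER

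*Protocol article*

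**What the plan says.** The Economic analysis section compares DCM with the QUALIDEM-based intervention and sets two ratios: "cost per increase in quality of life scores of the residents and cost per increase in attitudes toward dementia scores". On perspective it states: "The cost calculation will be performed from a societal point-of-view". It then adds: "Other outcome measures such as challenging behavior, job satisfaction, and burnout will be financially valued and computed on the cost side of the ICER". The text does not separate the two ratios here, so the rule applies to both.

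Table 1 classifies the same measures differently. The NPI-NH, the COPSOQ job satisfaction scale and the CBI burnout scale are secondary outcomes, and the only entry typed as a cost outcome is resource use. On data, the Measures section says: "Cost data for the economic evaluation will be extracted from the nursing home administrative system at the end of the intervention period". The Economic evaluation section adds that intervention costs, including DCM training, will be estimated.

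On how the outcomes relate to each other, the abstract says: "Most of the residents in nursing homes have challenging behaviors that strongly affect their Qol". The Background says that challenging behaviours "have a negative impact on stress levels and job satisfaction of the staff".

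**The concern.** An ICER divides incremental cost by incremental effect. It can be read because the numerator holds resources and the denominator holds one outcome in its natural unit. Giving other outcomes a money value and netting them against cost brings a cost-benefit step into that ratio. The figure then reflects three things: resources used, the effect, and the price someone attached to a point on another scale.

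A second problem concerns challenging behaviour in the quality-of-life ICER. If less challenging behaviour is part of why quality of life rises, the same improvement enlarges the denominator and, once priced, shrinks the numerator.

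Research question 5 rests on these ratios, and the article says that its results should inform the allocation of resources.

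**Working it through.** The article states no cost, unit price or ICER, so there is no figure to reproduce. The check has two parts.

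**1. The article's own statements side by side**

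- *What is priced.* NPI-NH runs from 0 to 144, job satisfaction from 1 to 4, burnout from 1 to 5 (Measures for people with dementia; Measures for caregivers). These are symptom and attitude scores, not quantities of resource.
- *Behaviour against the quality-of-life denominator.* The abstract states a strong effect of behaviour on quality of life. Content also overlaps: the Qol-AD covers mood, the NPI-NH covers depression, anxiety and apathy, and caregivers rate both. Overlap is therefore supported by the document.
- *Behaviour against job satisfaction, both in the numerator.* The Background links the two, so pricing both may count one effect twice within the numerator.
- *Job satisfaction or burnout against either denominator.* Nothing in the article says that these are the same benefit as resident quality of life or as the staff attitude score. Double counting is not shown here. Only the mixing of valuation methods applies.

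**2. How the ratio responds (all money figures and gains assumed, in arbitrary currency units)**

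Let ΔC be incremental resource cost, ΔE the gain in Qol-AD points, and B the money value given to the other outcomes (positive if they improve). Then

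planned ICER = (ΔC − B) / ΔE.

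Take ΔC = 1000 and ΔE = 2. On resources alone the ICER is 1000 / 2 = 500 per point.

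| B | Planned ICER |
|---|---|
| 250 | (1000 − 250) / 2 = 375 |
| 500 | (1000 − 500) / 2 = 250 |
| 1000 | (1000 − 1000) / 2 = 0 |
| 1500 | (1000 − 1500) / 2 = −250 |
| −500 (other outcomes worsen) | (1000 + 500) / 2 = 750 |

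Resources and quality of life are the same in every row; only B changes.

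To isolate double counting, let λ be the value of one Qol-AD point (assumed 400) and s the share of the quality-of-life gain that is the same benefit as the priced behaviour gain. Then B = s × λ × ΔE = s × 800, and net monetary benefit is NMB = λΔE − (ΔC − B). Counted once, NMB = 800 − 1000 = −200.

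| s | B | Planned ICER | Planned NMB |
|---|---|---|---|
| 0 | 0 | 500 | −200 |
| 0.25 | 200 | 400 | 0 |
| 0.5 | 400 | 300 | +200 |
| 1.0 | 800 | 100 | +600 |

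With no overlap nothing is counted twice. With overlap the conclusion can change sign although no benefit has been added.

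The reverse also holds. If quality of life falls by 2 points and half of that loss is also priced as behaviour, NMB moves from −800 − 1000 = −1800 to −800 − (1000 + 400) = −2200. The overlap exaggerates harm as readily as benefit.

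**The case against.** The strongest counter-argument is that the sentence may mean something legitimate. From a societal viewpoint, worse behaviour or more burnout can cost real money through care time, absence or turnover. Counting a health effect in the denominator and its true cost offset in the numerator is not double counting; a causal link alone does not make it so. On that reading the ratio is simply net cost per point. This stands as a possible meaning, and the article does not settle it. But the sentence assigns a value to the outcome measures themselves, and the fix below suits either reading.

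Several stronger inferences are tempting and are not supported:

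- *That all three outcomes are counted twice.* The article supports this only for behaviour against quality of life, and possibly for behaviour with job satisfaction inside the numerator.
- *That the ratio becomes uninterpretable.* Net cost per point can still be read. It is price-dependent and harder to compare with other ratios.
- *That the result is biased towards DCM.* The direction follows the secondary outcomes.
- *That no price list means an invented price.* A condensed article may leave the valuation method to a fuller plan, so its absence is no finding.
- *That the administration system is the sole cost input.* Intervention costs are also to be estimated, staff turnover is recorded in the DIQ every 3 months, and regular medication is collected.
- *That resource consequences would certainly be counted again.* The article does not list what the administration system holds.

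It is also fair to say that this is the fifth research question of a non-randomised study with three units per group, meant to inform a later randomised trial.

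**Conclusion.** The point holds in a limited form. As worded, the plan mixes cost-benefit valuation into both ICERs, so each depends on a price for scale scores. In the quality-of-life ICER it can also count the benefit of reduced challenging behaviour twice, given the link that the article states.

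The size cannot be derived from the article: it depends on the price and on the degree of overlap, and neither is given. The illustrations show only that the effect can be large enough to change the conclusion under assumed values.

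The verdict rests on taking the sentence at its word, as pricing the outcome measures. If only realised resource consequences were meant, the method is sound and the wording alone needs correction. The change should be made, but it does not affect the clinical effect analysis.

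**What to change.** Reword the Economic analysis section so that:

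- The ICER numerator holds intervention costs and observed resource use only. Real resource consequences of behaviour or burnout may be included where they are recorded (for example staff turnover from the DIQ), each counted once.
- NPI-NH, job satisfaction and burnout are reported in natural units beside the costs, in a cost-consequence table.
- Any money valuation of these scores appears only in a labelled sensitivity analysis.

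The change costs a few sentences and less work than the planned valuation. It needs no new data, and cost data are to be extracted only at the end of the intervention period. The small downside is that the main ICER no longer credits these outcomes in a single figure.

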## Study progress

The study design and protocol was approved by the Ethics Committee of the German Society of Nursing Science in August 2010. The collection of informed consent started in April 2011 and was followed by an informational kick-off event for the participating institutions. The assessment of baseline data occurred from July to September 2011. The last follow up measurements, effect and process evaluation, are scheduled for January to April 2013. Analysis of the data and dissemination of results are planned for autumn of 2013.

## Discussion

This quasi-experimental study will provide important information on the effects of DCM on residents and staff, implementation of DCM and cost-effectiveness of DCM in German nursing homes. The findings will be an important basis for the design of a subsequent randomized controlled trial.

DCM is a specific intervention with fixed elements and a defined implementation process. It is known that the implementation of DCM in an institution has a strong influence on residents and staff members, the health care team as a whole and the climate and management of an organization. The effects of DCM are strongly influenced by the interaction between the different levels of the organization and organizational readiness
[43]. For example, an interested team with motivated change-agents but with an adverse management might not be able to implement DCM to a degree that will result in an improvement of the Qol of the residents. Thus, in addition to the measurement of the intervention’s effects, a major focus of this study is the evaluation of the degree of implementation and the identification of main barriers to and facilitators of implementation. These findings will help nursing home decision-makers and managers decide whether to use DCM, and the results will help to design an adequate implementation process for DCM and other psychosocial interventions.

The following information will be generated and used in the design of a subsequent RCT on effectiveness of DCM in German nursing homes:

a. The appropriateness of the primary and secondary outcomes and important variables and their measurement.

b. Identification of characteristics of nursing homes and units that have a strong influence on the successful implementation of DCM. This information could be used to define inclusion criteria for nursing homes and units and to ensure maximum organizational readiness.

c. Information about helpful adaptations for the DCM implementation process.

d. Information about the treatment and control differences, attrition rate, standard deviation and the interclass correlation coefficient that is needed for a sample size calculation in a subsequent randomized controlled trial.

e. The subgroup analysis of control residents will give some indications about the spillover-effect of PCC on other residents who were not included in the DCM-cycle.

Overall, this study will provide novel data about the effectiveness and implementation process of DCM in German nursing homes. The study results will provide important information for the national discussion about the improvement of dementia-specific Qol, quality of care in nursing homes and the allocation of resources. The study will be important for decision-making and the design and implementation of complex psychosocial interventions such as DCM. Program implementation plans in nursing homes are often made on the basis of individual experience due to the absence of a body of knowledge about successful implementation strategies. Although our study has some design flaws, including a lack of randomization, it is the most feasible way to obtain firsthand data about the effectiveness and the implementation of DCM in German nursing homes.
